#### No Blinding and Potential Bias

Because patients know if they got a summary, their responses could be influenced by a sort of placebo or novelty effect; they might rate the communication highly out of gratitude or perception that they got extra care. Similarly, physicians know which patients got summaries and might unconsciously treat them a bit differently, perhaps spending a bit less time explaining basics. These are real possibilities. However, they are part of the intervention’s effect in a pragmatic sense—in real use, everyone would know the summary is given, and that itself could change behaviors; doctors in future might rely on these tools and adjust their approach accordingly. We opted for a pragmatic trial perspective: measure the outcome as it occurs with knowledge of the intervention. To gauge if bias is substantial, we will compare objective measure of time. If patients report much higher understanding but in reality asked many questions or time increased, we might consider that a bias in perception. We will triangulate data to judge this.

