### Randomization and Blinding

Randomization was performed using a computer-generated randomization list created prior to study start. The list was produced with a validated random number generator, fully covering the planned sample size for each trial (n=300). Assignments were generated in a 1:1 ratio (intervention vs control) and exported into a password-protected file with time-stamp documentation. The randomization list was stored on a secure hospital server, accessible only to the principal investigator and the designated study statistician. Allocation concealment was maintained because recruiting staff and treating physicians had no access to the sequence; group assignment for each newly enrolled participant was revealed sequentially through a locked module at the point of inclusion. This procedure prevents prediction of future allocations while ensuring reproducibility and auditability.

Due to the nature of the intervention, blinding is not possible for participants or treating physicians. Patients in the intervention arm will receive an additional written summary that is clearly different from standard documents, and physicians will likely recognize if a patient has an easy-summary or not (eg, patients might refer to it during the consult). We considered having a blinded outcome assessor, but our outcomes are primarily self-reported by patients and the treating physician immediately after their encounter, so blinding is not applicable. The study analysts will remain blind to group labels until after data analysis (groups will be coded as A and B during statistical analysis to prevent subconscious bias). While lack of blinding may introduce some risk of bias, outcomes such as questionnaire scores are less prone to observer bias and more a reflection of the participant’s genuine experience. We will compare certain objective measures (like consultation length) to see if any Hawthorne effect (change in behavior due to being studied) is present similarly in both groups.

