#### Secondary Outcome 4: Consultation Duration

We will record the length of the consultation (in minutes) from start to finish. In the outpatient setting, a research assistant will unobtrusively note the time the patient enters and leaves the doctor’s office. In the inpatient discharge setting, the time of the conversation with the doctor (often in the patient’s room or ward office) will be noted. This outcome addresses efficiency, as providing patients the summary could either increase time if patients ask more questions or discussion goes deeper, or decrease time if basic explanations need less repetition. Previous research offers mixed insights—sometimes better-informed patients make visits slightly longer due to more questions, but those questions may be more to the point, and satisfaction improves. We do not consider a modest change in time inherently negative; however, it is important to document if the intervention significantly alters physician time burdens. Our expectation is that consultation time might not differ greatly or could even decrease in the intervention group if clarification of basics is faster. This outcome is measured in a single-blind fashion, with the person timing is not influencing the interaction.

In addition to these main outcomes, we will collect exploratory data, for instance the number of questions patients ask during the consultation (not formally tallied, but physicians will provide a subjective rating of patient engagement) and any specific misunderstandings noted (physicians can report if they had to correct any wrong notions the patient had from reading the summary or otherwise). We will also debrief patients in the intervention group with a couple of questions about the summary itself (eg, “Did you find the AI-generated explanation helpful?” rated yes or no, and an open comment). These will be reported qualitatively to supplement interpretation, but they are not primary outcomes.

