### Comparison With Related Work

Our approach draws upon previous work in health literacy and patient education interventions. There have been efforts to rewrite medical documents in simpler language manually. For instance, Smolle et al [7] simplified discharge instructions, and found improved patient comprehension [7,8]. However, manual simplification is labor-intensive and not scalable in routine practice. The innovative aspect here is using AI (LLMs) to do this at scale and on-demand. Generative AI has only recently become capable enough to handle such tasks with reasonable accuracy. Zaretsky et al [8] provided evidence that an LLM (GPT-4 via Azure) can reliably simplify discharge summaries while maintaining content integrity. They did highlight safety concerns—in 18 of 100 reviews, physicians noted some missing or inaccurate information in AI outputs. This underscores the importance of having a human in the loop, as we have in our protocol. Our results will contribute real-world data on whether an AI-assisted workflow can be integrated feasibly without error-induced AEs.

Another related area is the use of patient question prompt lists or decision aids to improve communication. Those interventions provide patients with structured information and questions to consider, often leading to improved question-asking and involvement. Our AI summary could function similarly to a tailored information sheet; it might even prompt patients to ask about things they read. We will observe qualitatively if patients in the intervention ask more questions. If so, that could be an added benefit—engaged patients often lead to more accurate diagnoses and more concordant treatment plans [2].

In terms of health outcomes, our trials are not measuring long-term outcomes like adherence or health status. But literature ties improved communication to those outcomes. For example, a meta-analysis by Jahan and Siddiqui [14] found that good physician communication is associated with higher adherence to treatment (odds of adherence were 2.16 times higher when patients rated their physician’s communication as excellent). While beyond our scope, it is conceivable that if patients understand their condition and instructions better (through the summary and ensuing discussion), they will be more likely to follow medication and follow-up plans. We plan future research to track such outcomes.

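### Consultation time and questions asked cannot gauge bias in the unblinded self-reports, because the plan elsewhere treats the same signals as possible or welcome effects of the summary

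*Protocol article*

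**What the plan says.** Two places in the protocol article give consultation time a diagnostic role.

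- **No Blinding and Potential Bias** concedes that gratitude, novelty or altered physician behaviour could influence the results. It then says: "To gauge if bias is substantial, we will compare objective measure of time". The pattern that would raise suspicion follows: "If patients report much higher understanding but in reality asked many questions or time increased, we might consider that a bias in perception". The section closes by saying that the data will be triangulated.
- **Randomization and Blinding** plans a comparison of "certain objective measures (like consultation length) to see if any Hawthorne effect (change in behavior due to being studied) is present similarly in both groups". The list of safeguards against expectancy and performance bias in the same section includes, as item (3), objective endpoints such as consultation time, which are to complement the self-reports.

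Other sections describe the same signals as effects of the intervention. Under Secondary Outcome 4, "providing patients the summary could either increase time if patients ask more questions or discussion goes deeper"; a shorter visit is the other possibility named there. The number of questions is "not formally tallied, but physicians will provide a subjective rating of patient engagement". Comparison With Related Work adds: "We will observe qualitatively if patients in the intervention ask more questions", and says that such an increase could be a benefit.

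**The concern.** A check for bias is useful only if its signal behaves differently when the effect is real and when it is a reporting artefact. Here the suspicious pattern (better reported understanding together with more questions or a longer visit) is also one that the article describes when the summary works. A true gain in understanding that shows itself in a fuller conversation could then be written down as a perception artefact. Inflated ratings that leave visit length alone would go unnoticed.

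This matters because the patient-reported outcomes are unblinded, and the article offers the time comparison as its way of judging how large the resulting bias is. Without a fixed reading, the authors could also decide after seeing the data whether longer visits mean engagement or bias.

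**Working it through.** The plan gives no figure for this check, so the main work is to set the sections side by side.

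**1. The perception-bias reading**

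| Signal | No Blinding and Potential Bias | Elsewhere in the article |
|---|---|---|
| More questions, with higher understanding | Possible bias in perception | Intervention patients are encouraged to note their questions (Intervention section); patients who understand more are likelier to ask (Interpretation of the Intervention's Potential Impact); could be an added benefit (Comparison With Related Work) |
| Longer visit, with higher understanding | Possible bias in perception | A possible result of deeper discussion (Secondary Outcome 4); a minute or two more is arguably worth it if outcomes improve (Expected Outcomes and Future Directions) |

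The biases that the section itself names do not produce this signal. Gratitude and novelty act on the rating and need not alter minutes. Physicians who spend less time on basics would shorten the visit, the opposite of what the check looks for.

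**2. The data behind it.** Questions are not counted. The substitute is a physician's rating of engagement, and the Intervention section says that the physician knows the patient has the summary.

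**3. The Hawthorne comparison.** Both arms are studied. Both complete questionnaires (Control section), and timing applies without distinction of arm: in the outpatient trial "a research assistant will unobtrusively note the time the patient enters and leaves" the office. Let m be the usual mean time, h0 and h1 the effect of being studied in control and intervention, and s the summary's own effect.

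- Control mean = m + h0
- Intervention mean = m + h1 + s
- Difference = (h1 − h0) + s

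If h1 = h0, the effect of being studied cancels and only s remains, whatever its size. If h1 ≠ h0, only the sum is observed and the two parts cannot be told apart. A zero difference does not show that the effect is similar in both arms, since h1 − h0 and s may offset each other.

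**4. Illustration.** The operational rule and the effect sizes here are assumptions, not the plan's. The rule flags bias when understanding is significantly higher and time significantly longer in the intervention arm. The simulation used 150 per arm (Sample Size and Power Calculation), two-sided t tests at 0.05, SD 1, understanding and time drawn independently, and 4,000 runs.

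| Scenario | Flagged as bias |
|---|---|
| Real gain 0.5 SD, time +0.4 SD | 92% |
| Real gain 0.5 SD, time unchanged | 2.6% |
| Pure reporting bias 0.5 SD, time unchanged | 2.7% |
| Pure reporting bias 0.5 SD, time −0.3 SD | 0% |

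A direct calculation agrees. Power at 150 per arm is 0.991 for 0.5 SD and 0.932 for 0.4 SD, and 0.991 × 0.932 = 0.92. With time unchanged, the chance of a significant result in the longer direction is 0.025, and 0.991 × 0.025 = 0.025, whether the gain is real or not. The flag follows the effect on time and carries no information on whether the rating is biased.

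For the Hawthorne comparison, a shift of 1 SD in both arms gave a significant time difference in 4.6% of runs, against 4.8% with no shift.

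**The case against.** The case for leaving the text alone has real substance.

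- **The wording is tentative.** The article says that it might consider the pattern a bias and will triangulate. There is no decision rule, and the 92% belongs to a rule supplied for illustration. This stands: the check could mislabel a real benefit; it is not bound to.
- **The sentence concerns understanding, a secondary outcome.** The FAPI comparison under Statistical Analysis Plan is a two-group test that uses neither time nor questions. This stands. A reader might infer that the primary result would be overturned by longer visits, but the text does not say so. Only the general sentence about gauging bias reaches FAPI.
- **Longer visits are not the main expectation.** Secondary Outcome 4 expects little change or a decrease. This stands: longer time is a named possibility, whereas more questions are prompted and welcomed.
- **The Hawthorne sentence asks whether the effect is similar across arms, not whether it exists.** That is a fair reading, but the difference in time still mixes any differential effect with the summary's own. That sentence names consultation length only; questions play no part in it.
- **The pragmatic position is already stated.** The article accepts that knowledge of the summary is part of its effect. This is so, and it makes the bias check harder to justify.
- **Pairing subjective with objective endpoints is ordinary practice.** Agreed. Item (3) need not be deleted, but it does appear in a list of safeguards against expectancy bias, a role that time cannot fill.

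None of this gives time or questions the ability to detect expectancy.

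**Conclusion.** The concern holds in a limited form. The article reads higher understanding with more questions or longer visits as possible bias in one section and as a possible, acceptable or welcome effect in others. The check cannot separate the two, cannot detect gratitude or novelty effects that leave time unchanged, and has no question count behind it. The Hawthorne comparison fails for a related reason: a common effect cancels, and a differential one is confounded with the effect of the summary.

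A reader might also infer that equal visit times would be taken as proof of no bias. No section says this; the article describes only the suspicious pattern.

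The argument in the first three steps rests on the text alone. The percentages rest on the assumed rule, effect sizes and independence, and show direction rather than a forecast. Trial conduct and the primary FAPI analysis are untouched; what changes is what the authors may conclude about bias. Severity is minor to moderate.

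**What to change.** 1. In No Blinding and Potential Bias, remove the use of time and questions as a gauge of bias.
2. In Randomization and Blinding, remove the Hawthorne sentence. Reword safeguard (3) so that consultation time is a complementary outcome and not a protection against expectancy bias.
3. Report consultation time as the efficiency outcome described under Secondary Outcome 4, and the physician's engagement rating as unblinded and exploratory.
4. State in advance that the patient-reported outcomes measure perceived quality with knowledge of the summary, that the design cannot separate expectancy from benefit, and that time and question data will not be used to confirm or dismiss those results.

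The cost is text edits only, with no change to data collection, sample size or the primary test. The downside is that the article can no longer claim an objective check on bias.

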#### Single-Center, Single-Department Setting

Our sample comprises all neurosurgery patients, which may limit generalizability. Communication needs in neurosurgery might differ from, for example, internal medicine. Nonetheless, many issues, such as complex terms and short visits are universal. We deliberately included heterogeneity within neurosurgery, including spine issues, brain tumors, and other conditions across a broad adult age range, to obtain a diverse sample. Still, future multicenter trials in other fields would be valuable. For instance, applying this approach in primary care or oncology could be next steps. We anticipate our results will encourage such studies or implementations. Thus, while this study provides a proof-of-concept in neurosurgery, results may not directly extrapolate to other specialties. Future multicenter studies across diverse fields, such as oncology or primary care, are needed before broad implementation.

#### Risk of Workflow Disruption

Another important limitation is the risk of workflow disruption. Physicians may experience additional cognitive load from reviewing AI outputs, and patients may experience heightened anxiety if sensitive diagnoses are clearly stated. Furthermore, AI errors, even if rare, could undermine trust. These risks are integral to the evaluation and will be systematically monitored through the fidelity audit and AE reporting.

### Expected Outcomes and Future Directions

We anticipate that the Discussion section in the results paper will highlight improvements in the intervention group across most measures. If, for example, we find that patients with AI summaries have significantly higher FAPI scores, indicating a better perceived interaction, and that their understanding ratings are substantially better, it will provide direct evidence that understanding written information translates to feeling of better communication. We also expect to see a small improvement in satisfaction, which the FAPI captures, and autonomy support, as measured by the HCCQ, possibly moderately higher. We are very curious about the consultation length outcome. A noninferiority result, showing no significant increase in time, would be encouraging because it means such summaries do not slow down clinics. Even if time increases by a minute or two, if outcomes are improved, many would argue it is worth it, as that time might be offset by fewer phone calls later.

One intriguing possibility is that improved understanding could reduce decisional conflict. Although we are not formally measuring decisional conflict in this protocol, some FAPI items indirectly relate to whether patients felt involved in decisions. If analysis of those items, such as “The doctor and I made treatment decisions together,” shows higher agreement in the intervention group, that implies better SDM. This aligns with findings that information provision is a prerequisite for SDM.

After these trials, we foresee a need to evaluate longer-term outcomes. For example, do these better communication experiences lead to improved adherence to discharge instructions or follow-up attendance? Are there fewer calls to the clinic with questions, or less need for repeated explanations? We have heard anecdotal reports that patients often call days after discharge with questions indicating they did not grasp the discharge instructions. If our intervention works, those calls might be reduced; we may try to gather such data as an exploratory measure during the trial. Additionally, health outcomes such as blood pressure control, pain management, or recovery might indirectly benefit when patients truly understand their care plan. It would be worth examining specific cases, such as medication adherence after discharge; this could be a follow-up study. Some neurosurgery patients receive new medications, such as steroids or anticonvulsants, and comprehension of instructions for those is vital.

Another future direction is cost-effectiveness. Although this study is not an economic evaluation, if it shows improved outcomes, the next question is at what cost, or potentially savings? Given the minimal costs for AI text generation, the main cost is personnel time for review and implementation. If the approach reduces readmissions or unnecessary visits due to confusion, it could even be cost-saving. We will gather some data on postdischarge contacts that may feed into a later cost analysis.

Finally, our research contributes to the broader field of how digital tools can support health communication without replacing the human touch. We emphasize that this AI tool is not taking over the physician’s role; rather, it augments the communication process. This distinction is important in discussions about AI in medicine. By focusing on translation of language, we are using AI in a targeted, low-risk way that potentially yields high impact. The trials’ outcomes will inform not only this specific use case but also how acceptability of AI interventions is perceived by patients. If patient satisfaction remains high, or even improves, with an AI-assisted process, that bodes well for patient acceptance of other AI-supported health care tasks.

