**Conclusions:**

These pragmatic randomized controlled trials test a scalable AI intervention to strengthen understanding and interaction quality without adding clinician burden. If effective, AI-assisted layperson summaries could be integrated into routine workflows to advance health literacy and patient-centered care.

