### Statistical Analysis Plan

We will first describe the sample using summary statistics (means or medians for continuous variables, frequencies for categorical variables). The two trial populations (outpatient vs inpatient) will be described separately. Baseline characteristics will be compared between arms to ensure that randomization achieved balance; any significant differences will be noted and adjusted for in secondary analyses if needed.

For the primary outcome (FAPI score), we will compare the intervention and control group means using an independent-samples *t* test (or nonparametric Wilcoxon rank-sum test if the distribution is highly skewed, although previous studies suggest near-normal distribution). We will report the mean difference with 95% CI. The primary analysis will be carried out separately for each trial. However, since the interventions and outcomes are identical, we may also perform a pooled analysis across both trials to increase power, including an indicator for trial to account for any systematic differences in context. Our hypothesis test is 2-sided with α=0.05. We anticipate a positive difference (intervention > control).

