### Secondary Outcomes Analyses

HCCQ scores will be compared similarly using a *t* test. Understanding ratings, which are on a scale from 1 to 5, will be compared using a Mann-Whitney *U* test for ordinal data or by dichotomizing responses as “understood well” for ratings of 4 or 5 and “not well” for ratings of 1-3, followed by a chi-square test. DDPRQ-10 scores, which yield a numeric difficulty score, will be compared by *t* test; additionally, we may compare the proportion of encounters meeting a “difficult” threshold (there is no absolute cutoff in literature, but >30 on the original 0-100 scale is sometimes used). Consultation time (in minutes) is likely to be skewed; we will compare medians with a Wilcoxon test, and also compare proportion of consultations exceeding a certain length (eg, >15 minutes) using a chi-square test.

We will consider *P*<.05 as significant for the primary outcome. For secondary outcomes, *P* values <.01 or <.05 will be interpreted with caution due to multiple comparisons. We are not formally adjusting for multiplicity, given that outcomes are correlated; however, the pattern of results will be considered collectively. Effect sizes will be presented (Cohen *d* for continuous outcomes, odds ratios for categorical comparisons) to gauge practical significance.

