### Public Health and System Implications

Health literacy has been called “the currency of health” in modern health care. Germany, like many countries, has recognized the need to improve health literacy at a population level [1]. Our intervention is one piece of that puzzle—a tool that health care providers can use to ensure each patient, regardless of background, receives information in an understandable form. If our trials show positive results, it would support wider implementation of AI-generated patient-friendly documents across hospitals and clinics. This could be particularly impactful in systems with high patient throughput and limited time, such as busy outpatient practices. By making written communications clearer, the onus on the doctor to cover everything orally in limited time might lessen, as patients come in with some pre-understanding.

From a system perspective, one might worry that providing these summaries is extra work or cost. However, thanks to AI automation, once set up, generating a summary takes only seconds and could be triggered as part of the electronic health record workflow. The physician’s time to review the summary for accuracy is a few minutes—likely offset by time saved in repetitive explanations. And the cost of using the AI (computing cost) is minor per document—perhaps a few cents to a couple of euros depending on length and model pricing. There is also no external funding for this study, meaning this concept is being developed without pharmaceutical or large grant backing—a testament that it is a practical solution emerging from clinical need and tech opportunity, rather than a commercial product push. If effective, we imagine no difficulty in convincing hospital administrations to adopt it, given the relatively low cost and alignment with quality improvement goals (some countries might even incorporate it into guidelines for discharge processes to improve patient comprehension).

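### A non-significant increase in consultation time is treated as noninferiority and as evidence that clinics are not slowed, which it cannot show

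*Protocol article*

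**What the plan says.** Consultation duration is the fourth secondary outcome. It is timed from the start to the end of the encounter, and the stated reason is to document any effect on physicians' time (Secondary Outcome 4: Consultation Duration). The Results paragraph of the Abstract includes the hypothesis that consultations will not be lengthened excessively, without a number.

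For the analysis, Secondary Outcomes Analyses states: "Consultation time (in minutes) is likely to be skewed; we will compare medians with a Wilcoxon test". It adds that the authors will "also compare proportion of consultations exceeding a certain length (eg, >15 minutes) using a chi-square test". The promised effect sizes are Cohen d and odds ratios. A difference with an interval is promised for the primary outcome ("We will report the mean difference with 95% CI", Statistical Analysis Plan), but none is stated for time.

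Expected Outcomes and Future Directions then says how a null result would be read: "A noninferiority result, showing no significant increase in time, would be encouraging because it means such summaries do not slow down clinics". The next sentence reads in part: "Even if time increases by a minute or two, if outcomes are improved, many would argue it is worth it".

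On clinicians' time outside the consultation, Public Health and System Implications says that the physician's "time to review the summary for accuracy is a few minutes" and expects this to be recovered through less repeated explanation.

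**The concern.** The quoted sentence defines noninferiority as failure to find a significant increase, and then draws an operational conclusion from it. Under that criterion, the noisier the timing data, the easier it is to conclude that clinics are not slowed. A trial could report no slowdown while an increase of the size the article itself discusses is present and has not been excluded.

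The stated analysis does not rescue the reading. A rank-sum test compares medians only under extra assumptions, such as a pure shift between two distributions of the same shape. Clinic workload depends on total, and therefore mean, minutes. A significance test on the proportion of long consultations has the same limit: non-significance there does not bound the increase either.

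The hypothesis that consultations are not unduly lengthened is in the Abstract, so readers and hospital administrators are likely to look for this result.

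**Working it through.** **Inputs**
- 150 per arm in each trial, two-sided alpha 0.05 (Sample Size and Power Calculation).
- Increases of 1 and 2 minutes: the scale mentioned in Expected Outcomes and Future Directions. They are used for illustration and are not a margin set by the plan.
- SD of consultation time: not given. Assumed 5 to 10 minutes, with 4 and 12 as outer values. The only related figure is an average primary-care visit length of about 7 to 10 minutes (Introduction), which is neither an SD nor from neurosurgery.

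**1. The plan's own figure.** None is given for time. As a check of the formula on the primary outcome: n = 2 × (1.960 + 0.842)² × (SD/difference)² = 2 × 7.85 × (1.0/0.5)² = 62.8, so 63 per group, as stated.

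**2. Formulas for time (normal approximation)**
- SE = SD × √(2/150) = 0.1155 × SD; 95% CI half-width = 1.96 × SE.
- Probability of a non-significant result when the true increase is δ: Φ(1.96 − δ/SE).
- Power of a real noninferiority test with margin M and true difference zero (upper 95% limit below M): Φ(M/SE − 1.96). Number per arm for 80% power: 2 × 7.85 × (SD/M)².

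Example, SD 8 and δ = 2: SE = 0.924; 2/0.924 = 2.165; Φ(1.96 − 2.165) = Φ(−0.205) = 0.42.

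| Assumed SD (min) | CI half-width (min) | Non-significant, true +1 min | Non-significant, true +2 min | n per arm, 2-min margin | Power at 150 per arm, 2-min margin |
|---|---|---|---|---|---|
| 4 | 0.9 | 42% | 1% | 63 | 99% |
| 5 | 1.1 | 59% | 7% | 99 | 93% |
| 6 | 1.4 | 70% | 18% | 142 | 82% |
| 8 | 1.8 | 81% | 42% | 252 | 58% |
| 10 | 2.3 | 86% | 59% | 393 | 41% |
| 12 | 2.7 | 89% | 70% | 566 | 30% |

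For a 1-minute margin the number per arm is already 252 at SD 4.

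**3. The planned rank test.** Simulated lognormal times rounded to minutes, 150 per arm, 2,000 replicates per scenario, true mean increase 2 minutes:
- Proportional increase: non-significant in 5.5% (median 10, SD 4.5), 32% (median 15, SD 6.8), 41% (median 10, SD 7.9) and 54% (median 20, SD 9.0).
- Constant shift, same four settings: 1%, 18%, 13% and 42%.

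The planned test therefore gives the same picture as the approximation, and its sensitivity also depends on how the increase is distributed.

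**4. Medians and means.** A deliberately constructed case: both arms have median 12 minutes, with log-SD 0.4 in one and 0.7 in the other. The means are 12 × exp(0.4²/2) = 13.0 and 12 × exp(0.7²/2) = 15.3, a difference of 2.3 minutes. The Wilcoxon test was non-significant in 94% of 2,000 simulated trials.

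**5. Review time.** The outcome ends with the consultation. A few minutes of review per summary is at least as large as the differences above, occurs only in the intervention arm, and lies outside what is timed. Expected Outcomes and Future Directions calls personnel time for review and implementation the main cost. Risk of Workflow Disruption lists the load of reviewing as a risk, followed through the fidelity audit and adverse event reporting, with no mention of minutes.

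**The case against.** The sentence is a conditional remark in the Discussion about a secondary outcome. The analysis sections set no noninferiority hypothesis and no decision rule, and the outcome section allows for change in either direction. A reader might infer that the trial has committed itself to declaring noninferiority from a non-significant test; the documents do not go that far. A margin, or a Hodges-Lehmann shift in minutes to accompany the Wilcoxon test, may also stand in the analysis plan, which is not shown, so their absence from the article is not the error. What remains is that the article states a criterion that is wrong as written, and a margin elsewhere would contradict it rather than repair it.

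The sizes rest on an assumed SD. At 4 to 5 minutes a 2-minute increase would usually be detected. That is correct, and it is why a range is shown.

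Two further readings are tempting. One is that the article already accepts one or two extra minutes as its margin; it says only "Even if time increases by a minute or two, if outcomes are improved, many would argue it is worth it". The other is that the clinician-burden comparison is biased because review minutes are left out. The Abstract says the trials test whether the intervention can "strengthen understanding and interaction quality without adding clinician burden", but it does not define burden as consultation minutes, and the DDPRQ-10 also covers the physician's side. The article discloses review time, and in the trial the reviewer is a study team member, typically a physician or medically trained researcher, who need not be the consulting doctor (Intervention: AI-Based Translation). One summed clinician-time result is therefore not clearly the right quantity. Only a limit on what the duration outcome can support follows.

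**Conclusion.** The point holds in a limited form. Treating a non-significant increase as noninferiority, and as evidence that clinics are not slowed, is an invalid inference. With 150 per arm and an assumed SD of 5 to 10 minutes, a true 2-minute increase would be non-significant in about 7% to 59% of trials and a true 1-minute increase in about 59% to 86% (normal approximation). The simulated Wilcoxon results for 2 minutes are of similar order. Nothing stated for time gives a difference in minutes with an interval, so the stated analysis would not show which increases had been excluded.

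This should be fixed, but is not critical: it concerns one secondary outcome and one Discussion sentence, and the primary outcome, the randomization and the sample size calculation are unaffected.

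**What to change.** 1. Fix and justify a margin in minutes before data are seen. Report the difference in mean minutes with a 95% confidence interval (Welch or bootstrap), alongside the Wilcoxon and threshold analyses. Claim that consultations are not prolonged only if the upper limit is below the margin. Otherwise report the upper limit as the largest increase not excluded.
2. If no margin can be justified, delete the word noninferiority and the statement that clinics are not slowed, and report the estimate with its interval.
3. Describe the Wilcoxon test as a comparison of distributions rather than of medians.
4. Confine the time conclusion to consultation duration. Alternatively, add review minutes and the reviewer's role to the existing 12-item checklist, and report them next to the consultation-time comparison, not merged into it.

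**Cost.** The changes to wording and analysis are small, and the checklist fields are optional. The real price is that the claim becomes harder to make. At 150 per arm and a true difference of zero, a 2-minute margin would be met with probability 93%, 58% or 41% at SDs of 5, 8 or 10 minutes, and a 1-minute margin with about 41%, 19% or 14%. A 2-minute margin reaches about 80% power only if the SD is about 6 minutes or less. Review minutes must be logged as the reviews happen, since they cannot be recovered reliably afterwards.
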